## Abstract

**Introduction:**

Current intervention programme to improve drug adherence are either too complex or expensive for implementation and scale-up in low-middle-income countries. The aim of this study is to assess the process and effects of implementing a low-cost, targeted and tailored pharmacist intervention among patients with type 2 diabetes who are non-adherent to antihypertensive drugs in a real-world primary care Indonesian setting.

**Methods and analysis:**

A cluster randomised controlled trial with a 3-month follow-up will be conducted in 10 community health centres (CHCs) in Indonesia. Type 2 diabetes patients aged 18 years and older who reported non-adherence to antihypertensive drugs according to the Medication Adherence Report Scale (MARS) are eligible to participate. Patients in CHCs randomised to the intervention group will receive a tailored intervention based on their personal adherence barriers. Interventions may include reminders, habit-based strategies, family support, counselling to educate and motivate patients, and strategies to address other drug-related problems. Interventions will be provided at baseline and at a 1-month follow-up. Simple question-based flowcharts and an innovative adherence intervention wheel are provided to support the pharmacy staff. Patients in CHCs randomised to the control group will receive usual care based on the Indonesian guideline. The primary outcome is the between-group difference in medication adherence change from baseline to 3-month follow-up assessed by MARS. Secondary outcomes include changes in patients’ blood pressure, their medication beliefs assessed by the Beliefs about Medicines Questionnaire (BMQ)-specific, as well as process characteristics of the intervention programme from a pharmacist and patient perspective.

**Ethics and dissemination:**

Ethical approval was obtained from the Ethical Committee of Universitas Padjadjaran, Indonesia (No. 859/UN6.KEP/EC/2019) and all patients will provide written informed consent prior to participation. The findings of the study will be disseminated through international conferences, one or more peer-reviewed journals and reports to key stakeholders.

**Trial registration number:**

NCT04023734.

Strengths and limitations of this studyThe pharmacist-led intervention programme uses principles of targeting by screening for non-adherence and tailoring to the patients’ personal adherence problems to enhance its potential effect. Simple question-based flowcharts and an innovative adherence intervention wheel are provided to support the pharmacy staff.The intervention aligns with the current workflow and resources in the daily clinical practice of a lower-middle-income country and will not require a substantial change to the current care system.This study is designed as a cluster randomised controlled trial to reduce the risk of bias and contamination across study groups.The implementation process will be evaluated using the RE-AIM framework, which will enable us to carefully interpret the results and guide us when scaling up the intervention to include a larger population in Indonesia and other lower-middle-income settings.As is common with many behavioural intervention studies, it is not possible to blind the researchers and pharmacists to the group allocation of patients.

## Introduction

In patients with type 2 diabetes, the pharmacological treatment of comorbid hypertension can substantially reduce the risk of cardiovascular complications.^1^ However, although effective pharmacological treatment is available, adherence to antihypertensive medications in patients with type 2 diabetes is known to be suboptimal.^2^ Notably, non-adherence to antihypertensive medications is associated with poor health outcomes and increased healthcare costs.^3^ Therefore, effective intervention strategies to enhance adherence are urgently required.

Previous studies showed that patients may not take their medication for various reasons. Non-adherence could arise following a conscious decision after balancing the pros and cons of medication (intentional non-adherence), could be due to a lack of understanding of the medication regimen or due to forgetfulness (unintentional non-adherence).^4–7^ The reasons underlying intentional and unintentional non-adherence are not entirely independent and are heterogeneous. These reasons include lack of attention, lack of knowledge, high concerns and/or low necessity beliefs, which can reduce motivation.^4–7^ In addition, there may be other drug-related problems, such as difficulties with intake or high costs, that can lead to non-adherence.^8 9^ As such, there are no one-size-fits-all solutions to address non-adherence.

In developed countries with well-established healthcare systems, a wide variety of interventions to improve medication adherence have been developed.^10 11^ Six main types of interventions can be identified: patient education, medication regimen management, clinical pharmacist consultation, cognitive-behavioural therapies, medication-taking reminders and incentives to promote adherence.^11^ However, a Cochrane review showed that most interventions are often too complex and not particularly effective.^10^ Additionally, in lower-middle-income countries, the paucity of healthcare and economic resources poses challenges to proper implementation of adherence enhancing interventions.

Non-adherence may be more efficiently improved if only patients who need it are targeted and interventions are tailored to patients’ individual adherence barriers.^12 13^ Previous studies further suggested that effective interventions to improve adherence were led by a pharmacist, delivered face-to-face, administered directly to patients and behaviourally targeted compared with cognitively targeted interventions.^14^ In Southeast Asia, however, pharmacy services can be hampered by inadequate training of pharmacy staff.^15^ Furthermore, adherence interventions may not be sustained over time due to a lack of resources to maintain them. Thus, to improve adherence to antihypertensive drugs in patients with type 2 diabetes, a low-cost, targeted and tailored pharmacist-led intervention that can be integrated into the community pharmacy workflow is required.

The primary objective of this study is to assess the effect of a targeted and tailored pharmacist-led intervention on medication adherence to antihypertensive drugs among patients with type 2 diabetes. The secondary objectives are (a) to assess the effect of the intervention on blood pressure level and medication beliefs, (b) to evaluate the implementation of the intervention from a pharmacist and patient perspective and (c) to assess the effects of the intervention across different subgroups of patients.

## Methods and analysis

This protocol was developed in accordance with the CONSORT 2010 statement for cluster randomised trials^16^ and reported according to the SPIRIT checklist^17^ (online supplementary appendix A). We will use the RE-AIM framework^18^ to evaluate the implementation process of the intervention.

10.1136/bmjopen-2019-034507.supp1Supplementary data

### Study design and setting

This study is a 3-month cluster randomised controlled trial with two parallel arms and will be performed in Bandung City, Indonesia from August to December 2019 (figure 1). Clusters of randomisation are community health centres (CHCs), locally called *Puskesmas. Puskesmas* are primary healthcare centres at the subdistrict level, with each centre staffed with medical doctors, nurses, midwives, and pharmacists.

**Figure 1 F1:**
[figure not shown]
Consort flowchart. BP, blood pressure; BMQ-specific, Beliefs about Medicines Questionnaire-specific; CHC, community health centre; FGD, focus group discussions; MARS, Medication Adherence Report Scale.

### Participants

A total of 10 CHCs will be purposively selected based on a sufficient number of patients with type 2 diabetes with hypertension. The principal investigator (PI) will introduce and explain the study to the pharmacists and physicians in the CHCs. In each CHC, one pharmacist will be included. In Indonesia, one of the pharmacist’s responsibilities during routine clinical practice is to counsel patients with chronic diseases on their medication use, often performed in a counselling room that is separated from the drug counter.^19^ Screening for patients’ eligibility will be conducted by the pharmacist during regular outpatient visits. Once a patient is deemed eligible, the pharmacist will inform the PI or research assistant to approach the patient and briefly explain the study, and ask to sign informed consent (online supplementary appendix B). Patients will be eligible if they meet the following inclusion criteria: (i) at least 18 years old, (ii) diagnosed with type 2 diabetes for at least 1 year based on patient’s medical record, (iii) using at least one antihypertensive drug in the last 3 months, (iv) have signed informed consent and (v) have suboptimal medication adherence to antihypertensive drugs according to the Medication Adherence Report Scale (MARS score <20; MARS scores range from 5 to 25). Of note, our previous work in four regions in Indonesia (Bandung City, Yogyakarta City, Makassar City and Samarinda City) showed that half of the patients were non-adherent, with a MARS score <20. Patients with severe mental or physical constraints, pregnancy or in the lactation period, illiterate in the Indonesian language, enrolment in another intervention study and those not responsible for taking their own medication will be excluded.

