### Randomisation and blinding

We will use cluster randomisation at the CHCs level to reduce the risk of bias and contamination across study groups.^20^ The PI will randomise the CHCs into the intervention or control group in a 1:1 ratio. The randomisation sequence will be generated using a random number generator. Given the nature of the study design, both pharmacists and the PI cannot be blinded to the group assignment.

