### Intervention

Patients in the five CHCs randomised to the intervention group who were screened as non-adherent to their antihypertensive drugs will receive a tailored pharmacist-led intervention during two sessions (at baseline and at a 1-month follow-up) in addition to usual care. Both will be regular outpatient visits, when patients collect their medication. The intervention will be low cost, aligned with the current CHC workflow and will not require a substantial change to the current system. Before the study started, the intervention steps and materials were piloted in two pharmacies and optimised in an iterative process.

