#### Intervention at baseline (first session)

Before dispensing antihypertensive drugs during the first session, the pharmacist will discuss patient-specific barrier(s) for medication adherence based on their responses to the MARS questionnaire and three additional questions, which are derived from the Brief Medication Questionnaire^21^ (figure 2). The intervention strategy will then be tailored to the identified adherence problems. Based on the current literature,^22–24^ we defined four non-adherence problems that can be addressed by the community pharmacists, that is, (1) forgetfulness, (2) lack of knowledge, (3) lack of motivation and/or (4) other drug-related problems. Of note, patients might need a combined intervention strategy to address all experienced problems. The four non-adherence problems and recommended intervention strategies are specified in table 1. The session will end with involving patients in goal setting and writing the agreed goal at the top of the personalised leaflet. Pharmacists will remind patients to take his/her leaflet to the next visit.

**Table 1 T1:** Non-adherence problems and recommended intervention strategies

Non-adherence problems	Intervention strategies
1. Forgetfulness	Strategies to cope with forgetfulness include reminders, habit-based strategies and/or involvement of family members, and improving knowledge on what to do when a dose is forgotten.^23^ The use of a reminder tool or pill boxes will be encouraged and a reminder app can be implemented if the patient owns a mobile phone. The habit-based strategy will be delivered through a personalised leaflet, which is tailored to the patient’s daily routine (online supplementary appendix C). Patients will be asked to identify the appropriate place and time to take their medication, and an activity they conduct every day that could serve as a prompt or cue to take their medication.^31^ Patients will be asked to write coping plans to formulate their own ‘if–then’ plans for the daily doses of their antihypertensive drug(s).^31^ Moreover, patients will be asked to choose a family member to become their treatment supporter and to write down the name of a family member on the personalised leaflet. This individual will be asked to support the patient to take antihypertensive drugs. Pharmacists will keep a copy of the leaflet and remind patients to take his/her personalised leaflet to the next visit.

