### Control group

Patients in the five CHCs randomised to the control group will receive pharmacist counselling based on the Indonesian guideline of pharmacy practice (PMK No.74/2016).^19^ At each visit, they can receive information about the quantity and dose of the dispensed drugs, when and how to use and store the drugs, side effects and how to deal with them, the importance of medication adherence, and confirming if the patient understands how to take medications correctly. Patients in the control group who were screened as non-adherent to their antihypertensive drugs by the research assistant at baseline will complete the assessments at the same time points as those in the intervention group.

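### The text names different screeners for non-adherence in different places, so the MARS that gates entry, and very probably serves as baseline, could be obtained differently in the two arms

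*Protocol article*

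**What the plan says.** Three sections of the protocol article bear on who screens.

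- **Participants** (all CHCs): screening for "eligibility will be conducted by the pharmacist during regular outpatient visits". The fifth inclusion criterion is to "have suboptimal medication adherence to antihypertensive drugs according to the Medication Adherence Report Scale (MARS score <20; MARS scores range from 5 to 25"). The research team enters afterwards: "Once a patient is deemed eligible, the pharmacist will inform the PI or research assistant to approach the patient".
- **Control group**: control patients are those "screened as non-adherent to their antihypertensive drugs by the research assistant at baseline".
- **Intervention**: intervention patients are those "who were screened as non-adherent to their antihypertensive drugs will receive a tailored pharmacist-led intervention during two sessions". No screener is named. Under Intervention at baseline (first session), the pharmacist then discusses barriers "based on their responses to the MARS questionnaire and three additional questions".

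On masking, Randomisation and blinding states that "both pharmacists and the PI cannot be blinded to the group assignment". The Primary outcome section defines the endpoint as the between-group difference in MARS change from T0 to T2, with MARS answered by the patient. A blinded assessor is named only for blood pressure.

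**The concern.** Participants and Control group name different roles for finding non-adherent patients, and the corresponding sentence for the intervention arm names none. A site that follows the text literally would use the pharmacist in intervention CHCs, under the general rule, and the research assistant in control CHCs, under the arm-specific rule.

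Two routes to bias would follow.

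1. **Selection.** The intervention pharmacist must take the communication training and starts the intervention at the baseline session, so knows the CHC's arm by then. If that person decides who is put forward in one arm and an outsider does so in the other, the arms can recruit different patients. Randomising CHCs does not protect against this, although the article relies on the cluster design to limit bias.
2. **Measurement.** MARS is a self-report of missed doses. A patient may answer differently when the form comes from the pharmacist who dispenses the drugs than when it comes from an outsider. With a cut-off at 20, this also changes who passes the gate and how far scores regress towards the mean afterwards.

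Both routes lead into the change in MARS, which is the primary outcome.

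**Working it through.** **Step 1: the sections side by side.**

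| Section | Applies to | Who screens |
|---|---|---|
| Participants | all CHCs | pharmacist; PI or research assistant only after eligibility is judged |
| Control group | control CHCs | research assistant, for non-adherence, at baseline |
| Intervention | intervention CHCs | not named |

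If the pharmacist's screening includes the MARS criterion, Participants and Control group conflict. If it does not, the statement that the research team is called once the patient is judged eligible cannot be taken literally, because non-adherence would still be open. Either way at least one passage needs rewording.

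**Step 2: is the screening MARS the T0 MARS?** The Control group section places the screening at baseline. The first intervention session uses MARS answers at the T0 visit. No separate baseline MARS is described. The identity is therefore a strong inference, but it is not stated.

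**Step 3: reproduce the plan's sample size.** Inputs from Sample size calculation: difference 2.5, SD 3.8, ICC 0.014, 80% power, two-sided 5%.

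- Unclustered n per arm = 2 × [3.8 × (1.960 + 0.842) / 2.5]² = 36.27.
- Design effect with 10 patients per CHC = 1 + (10 − 1) × 0.014 = 1.126.
- 36.27 × 1.126 = 40.84, rounded up to 41, as stated.
- Recruitment: 100 screened per arm × 0.5 non-adherent × 0.8 retained = 40 analysed per arm, or 8 per CHC.

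**Step 4: standard error of the between-arm difference in change.**

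- 40 per arm, 8 per CHC: design effect = 1 + 7 × 0.014 = 1.098; SE = 3.8 × √(2 × 1.098 / 40) = 0.890.
- 41 per arm, 10 per CHC: SE = 3.8 × √(2 × 1.126 / 41) = 0.891.

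**Step 5: hypothetical illustration.** Assume that the screener shifts T0 MARS by b points in one arm only and that T2 is unaffected. The documents give no value for b. The contrast is then biased by b. With no true effect, the rejection rate comes from a noncentral t with noncentrality b / 0.890 and 10 − 2 = 8 df (critical value 2.306).

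| b | b / 2.5 | b / 0.890 | False-positive rate, t with 8 df | Same, normal reference |
|---|---|---|---|---|
| 0 | 0% | 0 | 5.0% | 5.0% |
| 0.5 | 20% | 0.56 | 7.9% | 8.7% |
| 1.0 | 40% | 1.12 | 16.8% | 20% |
| 1.5 | 60% | 1.68 | 31.8% | 39% |

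A shift in the opposite direction would hide a true 2.5-point effect: power on the normal reference falls from 80% to about 61%, 39% and 20%.

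**The case against.** The best defence is that a consistent reading exists. Participants never says who administers MARS. Signed consent is also on the list of inclusion criteria and is taken by the PI or assistant after the pharmacist's judgement, so the pharmacist cannot be checking every criterion. The pharmacist may pre-screen on age, diagnosis and drug use, with the assistant running MARS in both arms. The first intervention session is compatible with a form completed beforehand. The flowcharts and the counselling checklist are not shown and may name the screener. MARS also appears to be self-completed, since patients indicate their own answers and those illiterate in Indonesian are excluded, so no rater scores it.

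Much of this stands. A reader might infer that the pharmacist administers MARS to intervention patients, or that the plan deliberately measures the arms differently. No passage says either. A reader might also take the false-positive rates as estimates, but the shifts behind them are assumed. Nor is it a finding that no one is named to administer MARS at T2, since an article may leave that to the full protocol.

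The defence does not remove the conflict in wording. The consistent reading has to be supplied by the reader, and a site following the sentences as printed would use different screeners in the two arms. Self-completion removes rater scoring, but it does not remove the influence of who hands over the form or who chooses the patients to approach.

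**Conclusion.** The concern holds as an internal conflict that permits different screening by arm. It does not show that such screening is planned or that bias is present. It matters because the affected measurement is the entry gate and, very probably, the baseline of a self-reported primary outcome, and because the pharmacists are acknowledged to be unblinded.

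The size and direction of any bias cannot be derived from the documents. The range of about 8% to 32% for the false-positive rate holds only under assumed one-arm T0 shifts of 0.5 to 1.5 points, no effect on T2, the plan's SD of 3.8 and ICC of 0.014, 40 analysed patients per arm and a t reference with 8 df. The planned sample size is not in question here. Analysis cannot reliably repair differential recruitment afterwards, so the wording should be settled before enrolment.

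**What to change.** Reconcile Participants, Intervention and Control group to one procedure for all 10 CHCs:

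- The pharmacist may pre-screen on age, diagnosis and drug use.
- The research assistant, where possible unaware of the CHC's arm, then has consecutive patients complete MARS with the same script, before the pharmacist session.
- In intervention CHCs, the completed form goes to the pharmacist for tailoring.
- The text states whether this MARS is the T0 value.

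The cost is some research assistant time at visits. Assistants already approach patients for consent, record refusals and collect clinical data, so no new staff are needed, and the sample size does not change. One limit remains: the article does not say whether assistants are blinded. The change makes the two arms comparable in procedure, but it does not by itself guarantee blinded recruitment.

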### Randomisation and blinding

We will use cluster randomisation at the CHCs level to reduce the risk of bias and contamination across study groups.^20^ The PI will randomise the CHCs into the intervention or control group in a 1:1 ratio. The randomisation sequence will be generated using a random number generator. Given the nature of the study design, both pharmacists and the PI cannot be blinded to the group assignment.

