### Data management

Data from the questionnaires and case report forms will be entered by the PI using a unique identifier that is provided for each participant into SPSS software V.25 and data forms will be stored on a password-protected computer.

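### The unblinded PI allocates the health centres and may also consent patients, who appear to be recruited after their centre's arm is known, possibly with a different screener in each arm

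*Protocol article*

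**What the plan says.** **Allocation.** Randomisation and blinding: "The PI will randomise the CHCs into the intervention or control group in a 1:1 ratio". The next sentence adds that "The randomisation sequence will be generated using a random number generator", and the section closes by saying that "both pharmacists and the PI cannot be blinded to the group assignment". It also gives reduction of bias and contamination as the reason for randomising clusters.

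**Recruitment.** Participants: "Screening for patients’ eligibility will be conducted by the pharmacist during regular outpatient visits". Once a patient qualifies, "the pharmacist will inform the PI or research assistant to approach the patient and briefly explain the study, and ask to sign informed consent".

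**Timing.** The Intervention section speaks of patients screened as non-adherent within the five centres randomised to intervention, and places the first of two sessions at baseline. The description of that session has the pharmacist working from the patient's MARS answers.

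**Control arm.** The Control group section says that non-adherence in control patients is screened by the research assistant.

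**Data.** Data management: "Data from the questionnaires and case report forms will be entered by the PI", under a unique participant identifier.

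**Safeguards and disclosure.** Blood pressure is measured by a nurse blinded to group. The strengths and limitations list acknowledges that "it is not possible to blind the researchers and pharmacists to the group allocation of patients".

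**The concern.** In a cluster trial the centres are randomised but the patients are not. The arms are comparable at patient level only if patients enter in the same way on both sides. If those who find, approach or consent patients know the centre's arm, enrolment can differ between arms without anyone intending it. For example, more receptive patients might be enrolled where a counselling session is about to follow. A screener who differs by arm opens a second route, because the same patient might be classified or invited differently.

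The primary outcome is exposed. It is the change in a self-reported adherence score, and that change plausibly depends on motivation. The arms would then differ in expected change even if the intervention did nothing. Analysing patients as allocated does not help, because the difference arises at entry. A random effect for centre accounts for correlation within centres; it does not correct a systematic difference between arms.

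The protocol attributes the lack of blinding to the nature of the design. That is true of delivering the counselling. It is not true of drawing the allocation or asking for consent.

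**Working it through.** **1. Who does what**

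| Task | Role named | Section | Knows the arm? |
|---|---|---|---|
| Allocate centres | PI | Randomisation and blinding | Yes, stated |
| Screen, general text | Pharmacist | Participants | Yes, stated |
| Screen, control patients | Research assistant | Control group | Not stated for the role by name; the limitations list says researchers are unblinded |
| Approach and consent | PI or research assistant | Participants | PI yes; assistant as above |
| Enter questionnaires and forms | PI | Data management | Yes |
| Measure blood pressure | Nurse | Blood pressure level | No, stated |

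**2. Order of events.** The order is not dated and Figure 1 is not shown. However, screening is described inside centres already assigned to an arm, and session 1 uses the MARS answers at the baseline visit. An intervention pharmacist must therefore know the arm by the visit at which the patient is enrolled. Recruitment after allocation is the natural reading.

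**3. Screener.** Participants and Control group name different roles. Either the screener differs by arm or one of the two sections is wrong. They must be reconciled.

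**4. The plan's own sample size, as a check on the inputs** (Sample size calculation: difference 2.5, SD 3.8, ICC 0.014, two-sided 5%, power 80%).

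- Without clustering: 2 × [3.8 × (1.960 + 0.842) / 2.5]² = 36.27 per arm.
- Design effect with 10 patients per centre: 1 + (10 − 1) × 0.014 = 1.126.
- 36.27 × 1.126 = 40.84, rounded up to 41 per arm. This is the plan's figure.

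**5. Standard error of the difference at 41 per arm.**

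- Patients per centre: 41 / 5 = 8.2.
- Design effect: 1 + 7.2 × 0.014 = 1.1008.
- SE = 3.8 × √(2 × 1.1008 / 41) = 0.881 MARS points.

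**6. What an artefactual difference would do.** The documents give no size for selection bias, so the shift b is assumed and shown over a range. With no true effect, the chance of a significant result is

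P = Φ(−1.96 + b/SE) + Φ(−1.96 − b/SE).

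| Assumed b (MARS points) | Share of the 2.5-point target | b/SE | Error rate, normal | Error rate, t on 8 df |
|---|---|---|---|---|
| 0 | 0% | 0 | 5.0% | 5.0% |
| 0.25 | 10% | 0.284 | 5.9% | 5.7% |
| 0.5 | 20% | 0.568 | 8.8% | 7.9% |
| 1.0 | 40% | 1.136 | 20.6% | 17.1% |

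The last column uses the noncentral t distribution with 10 − 2 = 8 degrees of freedom, one observation per centre.

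**The case against.** The best defence has four parts.

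- **Disclosure.** The lack of blinding is listed as a limitation, blood pressure is measured blind, and the Process evaluation section already records age, gender and blood-pressure drugs of patients who refuse or leave, to compare responders with non-responders. This stands in part. The disclosure covers blinding but does not address recruitment after allocation, and the nurse protects only a secondary outcome.
- **Objective eligibility.** The criteria are explicit and include a numeric MARS cut-off. A reader might infer that pharmacists choose which eligible patients to refer. The text gives them no such discretion, so that inference goes too far. What remains is that the person applying the criteria is unblinded and may differ by arm.
- **Data entry.** A reader might infer that the PI could shape the primary result while entering it. MARS consists of closed items answered by the patient, so transcription leaves little room for judgement. This stands, and data entry is a minor part of the point. Data management also covers only questionnaires and case report forms; the protocol does not say who handles the focus-group data.
- **Silence in a condensed article.** The absence of a rule for consecutive recruitment cannot be held against it, since such detail commonly sits in the full protocol or its appendices. This stands, and the point does not rest on it. It rests on roles and timing that the article itself sets out.

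It is also true that assistants working at a centre where sessions begin at baseline will soon learn its arm, so masking them can only be partial.

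**Conclusion.** The concern holds as a stated design feature that carries an avoidable risk to the primary comparison. The unblinded PI allocates the centres and may consent patients. Recruitment appears to follow allocation. The two descriptions of screening disagree.

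The size of any bias is unknown. On the plan's SD, ICC and 41 patients per arm, assumed shifts of 0.25 to 1.0 point would raise the 5% error rate to between about 6% and 21% by the normal approximation, somewhat less with t on 8 degrees of freedom. This shows only that a modest bias, if present, would matter. The post-allocation timing is inferred, because the order is not dated and the flowchart is not shown.

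Two stronger readings are not supported. One is that the PI also picked the centres: the text says that centres are chosen purposively but not by whom, and gives the PI only the task of introducing the study to their staff. The other is that bias has been shown: the documents establish an open route and no more. The stated sample size is not affected.

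**What to change.** 1. Have someone with no role in recruitment allocate all 10 centres in one step, after all have agreed to take part.
2. Remove the PI from patient approach and consent. The existing research assistants approach every eligible patient by the same procedure in both arms, kept unaware of the arm as far as practicable.
3. Reconcile the Participants and Control group sections so that the same role screens with MARS in both arms.
4. Report by arm the numbers screened, with MARS below 20, refusing and enrolled, using the information already collected for the Process evaluation.
5. As a minor addition, enter data under a centre code that does not reveal the arm.

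The cost is protocol wording and some reassignment of tasks among existing staff, with less flexibility for the PI. Sample size, outcome and intervention are unchanged. Masking of the assistants will be imperfect once sessions start, but steps 1, 3 and 4 do not depend on it, nor does removing the PI from consent.
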